### 3.5 Summary of known and potential risks and benefits

Please use section 4.8 of the Wockhardt UK Ltd dated 31st March 2008 SmPC for prednisolone tablets. Please see Appendix 2 for Prednisolone Expected Adverse Events. IMPs will only be used for trial subjects.

### 3.6 Trial conduct

This trial will be conducted in compliance with the protocol, Good Clinical Practice (GCP) and the applicable regulatory requirements.

## 4. TRIAL DESIGN

### 4.1 Introduction

Design: PREDNOS 2 will be conducted as a phase III randomised parallel group, placebo-controlled, double-blind trial.

Population to be studied: Children with relapsing SSNS ( $\geq 2$  relapses in preceding 12 months).

Active treatment arm: Prednisolone 15mg/m^2/day as a single morning dose for six days commenced within 24 hours of the criteria for an URTI being met.

Control arm: Placebo (identical number of tablets) as a single morning dose for six days commenced within 24 hours of the criteria for an URTI being met.

### 4.2 Inclusion criteria

Subjects aged over 1 year and less than 19 years will be eligible for inclusion if they have relapsing SSNS, defined as **having experienced 2 or more relapses in the preceding 12 months**. This will include the following groups:

- Subjects on no long-term immunosuppressive therapy;
- Subjects receiving long term maintenance prednisolone therapy at a dose of up to and including 15mg/m^2 on alternate days;
- Subjects receiving long term maintenance prednisolone therapy at a dose of up to and including 15mg/m^2 on alternate days in conjunction with other immunosuppressive therapies, including levamisole, ciclosporin, tacrolimus, MMF, mycophenolate sodium and azathioprine;
- Subjects receiving long-term immunosuppressive therapies, including levamisole, ciclosporin, tacrolimus, MMF, mycophenolate sodium and azathioprine without long term maintenance prednisolone therapy.
- Subjects who have previously received a course of oral or intravenous cyclophosphamide:
  - Must have experienced two relapses in the 12 months prior to randomisation (in keeping with all other subjects)
  - Must have experienced at least one of these relapses following completion of cyclophosphamide therapy
  - Must be at least 3 months post completion of oral or intravenous cyclophosphamide therapy.
- Subjects who have previously received a single dose or course of intravenous rituximab:

- Must have experienced two relapses in the 12 months prior to randomisation (in keeping with all other subjects)
- Must have experienced at least one of these relapses following completion of rituximab therapy
- Must be at least 3 months post completion of intravenous rituximab therapy.
- Parents and (where age appropriate) subject understand the definition of URTI and the need to commence study drug once this definition has been met.
- Written informed consent obtained from the subject's parents/guardians and written assent obtained from subject (where age appropriate). Subjects aged 16 years and above will provide their own written informed consent.

It is expected that there will be relatively even representation of subjects across the four background therapy groups (no background immunosuppressive therapy, long term maintenance prednisolone therapy, long term maintenance prednisolone therapy plus other immunosuppressive therapies, other immunosuppressive therapies alone), but this will be monitored during the trial. There is no evidence to suggest that the incidence of URTI is different with any one treatment regimen compared with the others, or that the likelihood of URTI precipitating a relapse of nephrotic syndrome differs according to this background immunosuppressant therapy.

#### 4.3 Exclusion criteria

- Subjects with steroid resistant nephrotic syndrome
- Subjects receiving, or within 3 months of completing a course of oral or intravenous cyclophosphamide
- Subjects receiving, or within 3 months of receiving a course of rituximab
- Subjects on daily prednisolone therapy at time of recruitment
- Subjects on a prednisolone dose of greater than 15mg/m^2 on alternate days at the time of recruitment\*
- Subjects with a documented history of significant non-adherence with medical therapy
- Subjects who will be transferred from paediatric to adult services during the 12 month study period
- Subjects unable to take prednisolone tablets, even in crushed form
- Known allergy to prednisolone

\*This applies to dose of prednisolone at the time of randomisation only. If prednisolone dose increases during the 12 month study period e.g. after a relapse, subject may remain in the study.

#### 4.4 Randomisation and allocation concealment

Following the informed consent process, which will be conducted in accordance with current GCP [Medical Research Council], and completion of the baseline assessments, subjects will be randomised at the level of the individual on a 1:1 basis to either the **active treatment** or **control** arm. Randomisation will be provided by a computer generated programme at the Birmingham Clinical Trials Unit (BCTU). The randomisation will be stratified by the treatment regimen that the subject is receiving at randomisation (no treatment; long term maintenance prednisolone therapy only; long term maintenance prednisolone therapy with other immunosuppressant therapy; other immunosuppressant

therapy only). Treatment allocation will only be revealed to the central pharmacy dispensing the study drug at Birmingham Children's Hospital.

Study drug will be manufactured, packed and labelled by Essential Nutrition. Following randomisation, subjects will be provided with a supply of 100 tablets (2 containers of 50 tablets) of study drug (prednisolone 5mg for those randomised to the **active treatment arm** or matching placebo for those randomised to the **control arm**). This will be sent directly to the family home from the central pharmacy at Birmingham Children's Hospital by Royal Mail Special Delivery on a day convenient for the family. The study drug containers and their contents will appear identical in every way, thus maintaining the double-blind. Study drug labelling will comply with the applicable regulatory requirements and clinical trial specific labels will be attached to all treatment. Birmingham Children's Hospital Pharmacy will maintain drug accountability logs for dispensed and returned study drug according to their local policy. Central pharmacy at Birmingham Children's Hospital must document when contacted by the parent/patient to confirm receipt of IMP, as below.

Every subject participating in the study will also be issued with a standard pack containing:

- i. Subject diary in which the results of the morning urinalysis, treatment administration and any consultations with healthcare professionals (GP, nurse, hospital A+E department etc.), development of URTI, commencement of study drug and details of medicines prescribed or purchased over the counter are to be recorded.
- ii. Instructions on contacting the central pharmacy at Birmingham Children's Hospital on receipt of IMP at the family home. This will include date of receipt and number of bottles received.
- iii. Electronic tympanometric thermometer to measure temperature at the time of suspected URTI (see below).
- iv. Written and (if requested) electronically downloadable information regarding URTI definition.
- v. Written and (if requested) electronically downloadable information regarding dose of study drug to be commenced in the event of URTI developing.
- vi. Other 'aide memoirs' regarding definition of URTI etc. displayed on fridge magnets and laminated sheets.

#### 4.5 Planned interventions

Current practice is for no change to be made to immunosuppressive therapy at the time of development of an URTI. The intervention being assessed within PREDNOS 2 is a 6 day course of daily prednisolone therapy at the time of onset of URTI.

Those randomised to the **active treatment arm** will commence on a 6 day course of daily prednisolone each time they develop an URTI (see below for strict definition) during the 12 month follow-up period. Those randomised to the **control arm** will receive an identical number of placebo tablets, thus allowing double blinding of the study. If the subject is receiving background long-term immunosuppressive therapy (e.g. levamisole, ciclosporin), then this should continue unchanged (see section 4.8).

#### 4.6 Definition of an Upper Respiratory Tract Infection

An URTI will be defined as the presence of at least 2 of the following *for at least 24 hours*:

- sore throat
- ear pain/discharge
- runny nose
- cough (dry/barking)
- hoarse voice
- fever >37°C (measured using tympanometric electronic thermometer)

Parents will be provided with clear written and (if requested) downloadable electronic information informing them of the study definition of an URTI as outlined above. They will also be provided with abbreviated versions of these printed onto laminated cards which can be kept in multiple locations within the family home including in fridge magnet format. An electronic tympanometric thermometer (Braun thermoscan) will be provided to the parents of all subjects to allow them to measure their child's temperature. A study diary will also be provided for parents to record the results of the daily morning urinalysis (standard care in children with relapsing SSNS), development of URTI, commencement of study drug, other ongoing treatment, acute illnesses and other issues.

#### 4.7 Commencement of study drug

Once the subject meets the definition for URTI (two or more criteria for at least 24 hours), the parents will commence their child on study drug (prednisolone 5mg tablets for those in the **active treatment arm** or placebo for those in the **control arm** according to randomisation). The precise dosing regimen will have been calculated at the baseline study visit at the time of their recruitment and will be reviewed at each study visit, or between study visits if there is a change in the dose of long term maintenance prednisolone therapy. Information about the precise number of study drug tablets to administer will be provided for the family in written form, using a standard form (Advice Letter to Parent/Participants) which will be completed by the investigator. Please ensure that a copy of the Advice Letter to Parent/Participants is copied and filed in the patient notes and site file. This information is considered as usual clinical information and as such should also be recorded in the patient notes. At each assessment please recalculate the study tablets needed if the patient develops an URTI, and as necessary if the subject's height, weight, body surface area or background prednisolone therapy has changed. Please use the Dose Calculator on the online system and complete numbers in the Advice Letter to Parent/Participants. If a new Advice Letter to Parent/Participants is issued again please copy and file in the patient notes and site file and record the information in the patient notes.

It is anticipated that parents will have no difficulties in identifying that their child has met the URTI criteria and will be happy to commence study drug unassisted, having been provided with comprehensive advice at the time of their recruitment. However, to provide a secure back-up service in case of any doubt, parents will be instructed to contact their local study site, or in case this is not possible, a PREDNOS 2 study telephone number will be provided to the parents of all study subjects. This will be manned by the Chief Investigator or his nominated deputy during periods of annual leave etc. Parents will be able to seek advice regarding whether their child meets URTI criteria, the dose of study drug required, or any other issues relating to the study. A log of these telephone calls will be maintained, and the Chief Investigator will report their content to the local Principal Investigator by email.

To ensure patient safety, the information provided to parents will also contain information about signs of more serious infection (non-blanching rash, leg pain, cool extremities, rapid breathing, blue lips, fitting, unconsciousness or any other major concern). If any of these features are present, parents will be instructed not to start study drug and to seek urgent medical attention for their child from their GP or local Accident and Emergency Department.

Parents will be asked to contact their local study site before or within 24 hours of commencing study drug to inform the Principal Investigator or nominated deputy and to allow them the opportunity to discuss any of their child's symptoms that may be of concern to them. Please ensure, in accordance with GCP, that all contacts with parents/patients are recorded in the patient's medical notes, including telephone and email contacts. Paediatric centres regularly receive a significant number of telephone calls from the parents of children with SSNS as part of routine clinical care (e.g. for advice on the management of disease relapses, requests for information following exposure to infections etc.). Parents of children with SSNS all routinely perform regular and careful home-based monitoring of their child's condition, including daily urinalysis and monitoring for exposure to and development of infection. They are instructed to contact the paediatric centre when proteinuria recurs or whenever there are other concerns and thus the telephone call for the purpose of this study will represent a simple extension of this well established practice, but must be recorded in the medical notes.

**This process should be repeated every time the child develops an URTI over the 12 month follow-up period. The only exception to this is if the child is receiving daily prednisolone therapy e.g. in the early stages of treatment for a previous relapse – in this instance study drug should not be commenced.**

#### **4.8 Dosing of study drug**

The number of tablets of study drug (prednisolone 5mg for those in the **active treatment arm** and matching placebo for those in the **control arm**) to be administered once URTI develops will be calculated at the time of the baseline (randomisation) visit and will be reviewed at each subsequent visit, to allow any adjustment necessary because of changes in the child's body surface area or long term maintenance prednisolone dose.

#### ***1] Subjects not receiving long term maintenance prednisolone therapy at time of development of URTI***

Subjects should receive a total number of study drug tablets equivalent to a prednisolone dose of 15mg/m^2 (maximum dose 40mg) for a total of 6 days given as 5mg tablets. Dosing should be rounded up or down to the nearest 5mg (maximum dose 40mg).

#### **Example 1: A subject with a body surface area of 1.0 m^2.**

Note: Body surface area is frequently used for drug dosing in paediatric practice and is most simply calculated using the Mosteller formula  $BSA = \sqrt{(\text{height} \times \text{weight} / 3600)}$  [Mosteller, 1987].

Prednisolone dose = 15mg daily for 6 days = 3 x 5mg tablets daily for 6 days

Subject should therefore receive 3 tablets of study drug (prednisolone for those in the **active treatment arm** or placebo for those in the **control arm**) for 6 days.

**Example 2: A subject with a body surface area of 1.2m^2**

Prednisolone dose = 18mg daily for 6 days, rounded up to 20mg daily for 6 days = 4 x 5mg tablets daily for 6 days

Subject should therefore receive 4 tablets of study drug (prednisolone for those in the **active treatment arm** or placebo for those in the **control arm**) for 6 days.

**Example 3: A subject with a body surface area of 0.8m^2**

Prednisolone dose = 12mg daily for 6 days, rounded down to 10mg daily for 6 days = 2 x 5mg tablets daily for 6 days

Subject should therefore receive 2 tablets of study drug (prednisolone for those in the **active treatment arm** or placebo for those in the **control arm**) for 6 days.

**Study drug should always be given as a single dose in the morning.**

**Co-administration of other immunosuppressive and other medications**

If the subject is receiving an additional immunosuppressive therapy e.g. ciclosporin, levamisole etc., this should continue unchanged throughout the six day course of study drug. Other drug treatment should also continue unchanged.

**At the end of the 6 day course of study drug**, the subject should continue as previously, i.e. taking no prednisolone. Other drug treatment should continue unchanged.

The study drug dose to be used on development of an URTI may change during the study due to alterations in the subject's long-term maintenance prednisolone dose and normal childhood growth. The precise regimen to be administered will be discussed with parents along with a written treatment plan at the time of recruitment and (in light of the above) will be re-discussed at each study visit. Where changes in long term maintenance prednisolone dose occur between study visits (e.g. as part of a planned reducing regimen), updated information will be sent to parents by mail or email. Parents will always have clear written instructions to inform them of the precise regimen of study drug to give to their child should they develop an URTI.

***2] Children receiving long term maintenance prednisolone therapy at a dose of less than 15mg/m^2 on alternate days at time of development of URTI***

Subjects should receive a total number of study drug tablets equivalent to a prednisolone dose of 15mg/m^2 (maximum dose 40mg) given as 5mg tablets. Dosing should be rounded up or down to the nearest 5mg (maximum dose 40mg).

**Example 1: A subject with a body surface area of 1.0 m^2 receiving a long term maintenance prednisolone dose of 10mg (10mg/m^2) on alternate days**

Note: Body surface area is frequently used for drug dosing in paediatric practice and is most simply calculated using the Mosteller formula  $BSA = \sqrt{(\text{height} \times \text{weight} / 3600)}$  [Mosteller, 1987].

At development of URTI, subject commences on study drug (5mg prednisolone or placebo) as follows so that the prednisolone dose received in the active treatment arm is 15mg/m^2 (equivalent to 15mg in this case) and those in the control arm receive an identical number of tablets, thus maintaining the double blind.

If day of commencement of study drug is a day when regular maintenance prednisolone is due,

Day 1 Prednisolone 10mg + 1 tablet of study drug

Day 2 3 tablets of study drug

Day 3 Prednisolone 10mg + 1 tablet of study drug

Day 4 3 tablets of study drug

Day 5 Prednisolone 10mg + 1 tablet of study drug

Day 6 3 tablets of study drug

If day of commencement of study drug is not a regular treatment day then,

Day 1 3 tablets of study drug

Day 2 Prednisolone 10mg + 1 tablet of study drug

Day 3 3 tablets of study drug

Day 4 Prednisolone 10mg + 1 tablet of study drug

Day 5 3 tablets of study drug

Day 6 Prednisolone 10mg + 1 tablet of study drug

This regimen will result in subjects randomised to the active treatment arm receiving prednisolone 15mg daily for 6 days and those randomised to the control arm undergoing no change in their therapy.

**Example 2: A subject with a body surface area of 1.2m^2 receiving a long term maintenance prednisolone dose of 10mg (8.3mg/m^2) on alternate days**

Note: Body surface area is frequently used for drug dosing in paediatric practice and is most simply calculated using the Mosteller formula  $BSA = \sqrt{(\text{height} \times \text{weight} / 3600)}$  [Mosteller, 1987].

At development of URTI, subject commences on study drug (5mg prednisolone or placebo) as follows so that the prednisolone dose received in the active treatment arm is 15mg/m^2 (equivalent to 20mg in this case – precise dose is 18mg, though rounded up to 20mg) and those in the control arm receive an identical number of tablets, thus maintaining the double blind.

If day of commencement of study drug is a day when regular maintenance prednisolone is due,

Day 1 Prednisolone 10mg + 2 tablets of study drug

Day 2 4 tablets of study drug

Day 3 Prednisolone 10mg + 2 tablets of study drug

Day 4 4 tablets of study drug

Day 5 Prednisolone 10mg + 2 tablets of study drug

Day 6 4 tablets of study drug

If day of commencement of study drug is not a regular treatment day then,

Day 1 4 tablets of study drug

Day 2 Prednisolone 10mg + 2 tablets of study drug

Day 3 4 tablets of study drug

Day 4 Prednisolone 10mg + 2 tablets of study drug

Day 5 4 tablets of study drug

Day 6 Prednisolone 10mg + 2 tablets of study drug

This regimen will result in subjects randomised to the active treatment arm receiving prednisolone 20mg daily for 6 days and those randomised to the control arm undergoing no change in their therapy.

**Example 3: A subject with a body surface area of  $0.8\text{m}^2$  receiving a long term maintenance prednisolone dose of  $10\text{mg}$  ( $12.5\text{mg}/\text{m}^2$ ) on alternate days**

Note: Body surface area is frequently used for drug dosing in paediatric practice and is most simply calculated using the Mosteller formula  $\text{BSA} = \sqrt{(\text{height} \times \text{weight} / 3600)}$  [Mosteller, 1987].

At development of URTI, subject commences on study drug (5mg prednisolone or placebo) as follows so that the prednisolone dose received in the active treatment arm is  $15\text{mg}/\text{m}^2$  (equivalent to 10mg in this case – precise dose is 12mg, though rounded down to 10mg) and those in the control arm receive an identical number of tablets, thus maintaining the double blind.

If day of commencement of study drug is a day when regular maintenance prednisolone is due,

Day 1 Prednisolone 10mg + 0 tablets of study drug

Day 2 2 tablets of study drug

Day 3 Prednisolone 10mg + 0 tablets of study drug

Day 4 2 tablets of study drug

Day 5 Prednisolone 10mg + 0 tablets of study drug

Day 6 2 tablets of study drug

If day of commencement of study drug is not a regular treatment day then,

Day 1 2 tablets of study drug

Day 2 Prednisolone 10mg + 0 tablets of study drug

Day 3 2 tablets of study drug

Day 4 Prednisolone 10mg + 0 tablets of study drug

Day 5 2 tablets of study drug

Day 6 Prednisolone 10mg + 0 tablets of study drug

This regimen will result in subjects randomised to the active treatment arm receiving prednisolone 10mg daily for 6 days and those randomised to the control arm undergoing no change in their therapy.

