| Treatment Description/Arms | 
Active treatment arm: Daily prednisolone for a total of 6 days commenced once criteria for URTI have been met.
 
Control arm: Daily placebo for a total of 6 days commenced once criteria for URTI have been met.
 
An URTI will be defined as the presence of at least 2 of the following for at least 24 hours:
 
 
• sore throat
 
• ear pain/discharge
 
• runny nose
 
• cough (dry/barking)
 
• hoarse voice
 
• fever >37°C (measured using tympanometric electronic thermometer)
 
 
Subjects who are receiving a long term maintenance prednisolone dose of up to and including 15mg/m^2 on alternate days (including those not on maintenance prednisolone therapy) at the time of development of URTI will receive the following;
 
Active treatment arm - prednisolone 15mg/m^2 daily for a total of six days, through the use of additional prednisolone study drug tablets.
 
Control arm – No change to therapy through the use of placebo study drug tablets for a total of six days.
 
For example, if a subject is receiving a long term maintenance prednisolone dose of 10mg/m^2 on alternate days, for those subjects randomised to the active treatment arm, the dose will be increased to 15mg/m^2 daily for a total of six days. Those in the control arm will receive prednisolone 10mg/m^2 on alternate days, with placebo tablets being administered to increase the total number of tablets so that it is identical to that being administered in the active treatment arm.
 
Subjects who are receiving a prednisolone dose of greater than 15mg/m^2 on alternate days at the time of development of URTI will receive the following;
 
Active treatment arm - prednisolone at alternate daily dose given daily for a total of six days, through the use of additional prednisolone study drug tablets
 
Control arm – No change to therapy through the use of placebo study drug tablets for a total of six days.
 |

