### ***3] Children receiving prednisolone therapy at a dose of greater than 15mg/m^2 on alternate days at the time of development of URTI***

Note – this will represent the minority of study subjects, as one of the key exclusion criteria for randomisation is subjects receiving a prednisolone dose which is greater than 15mg/m^2 on alternate days. There will, however, be subjects who develop a disease relapse (either URTI related or non-URT I related) during the course of the 12 month study and may therefore be receiving a higher dose of prednisolone at the time of development of an URTI. This could be the first URTI, around which the primary end point of the study is based, or a subsequent URTI. The management should be the same in both instances and is as follows;

Subjects should receive a total number of study drug tablets equivalent to the alternate daily prednisolone dose being received (maximum dose 60mg) given as 5mg tablets. Dosing should be rounded up or down to the nearest 5mg (maximum dose 60mg).

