#### **Example 1: A subject with a body surface area of 1.0 m^2 receiving a prednisolone dose of 20mg (20mg/m^2) on alternate days**

Note: Body surface area is frequently used for drug dosing in paediatric practice and is most simply calculated using the Mosteller formula  $BSA = \sqrt{(\text{height} \times \text{weight} / 3600)}$  [Mosteller, 1987].

At development of URTI, subject commences on study drug (5mg prednisolone or placebo) as follows so that the daily prednisolone dose received in the active treatment arm is equivalent to the current alternate daily dose – 20mg/m^2 (equivalent to 20mg in this case) and those in the control arm receive an identical number of tablets, thus maintaining the double blind.

If day of commencement of study drug is a day when regular maintenance prednisolone is due,

Day 1 Prednisolone 20mg + 0 tablets of study drug

Day 2 4 tablets of study drug

Day 3 Prednisolone 20mg + 0 tablets of study drug

Day 4 4 tablets of study drug

Day 5 Prednisolone 20mg + 0 tablets of study drug

Day 6 4 tablets of study drug

If day of commencement of study drug is not a regular treatment day then,

Day 1 4 tablets of study drug

Day 2 Prednisolone 20mg + 0 tablets of study drug

Day 3 4 tablets of study drug

Day 4 Prednisolone 20mg + 0 tablets of study drug

Day 5 4 tablets of study drug

Day 6 Prednisolone 20mg + 0 tablets of study drug

This regimen will result in subjects randomised to the active treatment arm receiving prednisolone 20mg daily for 6 days and those randomised to the control arm undergoing no change in their therapy.

**Example 2: A subject with a body surface area of  $1.2\text{m}^2$  receiving a prednisolone dose of 25mg ( $20.8\text{mg}/\text{m}^2$ ) on alternate days**

Note: Body surface area is frequently used for drug dosing in paediatric practice and is most simply calculated using the Mosteller formula  $\text{BSA} = \sqrt{(\text{height} \times \text{weight} / 3600)}$  [Mosteller, 1987].

At development of URTI, subject commences on study drug (5mg prednisolone or placebo) as follows so that the daily prednisolone dose received in the active treatment arm is equivalent to the current alternate daily dose –  $20.8\text{mg}/\text{m}^2$  (equivalent to 25mg in this case) and those in the control arm receive an identical number of tablets, thus maintaining the double blind.

If day of commencement of study drug is a day when regular maintenance prednisolone is due,

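### Protocol 4.8: the rule sentences for children on alternate-day prednisolone leave out the background dose, whereas every worked example and the Synopsis count it towards the target

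*Combined protocol and SAP*

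**What the plan says.** Protocol 4.8 sorts children by the prednisolone they are taking when a URTI develops: (1) no long-term maintenance, (2) maintenance below 15 mg/m² on alternate days, (3) more than 15 mg/m² on alternate days, (4) daily prednisolone, for whom study drug is not started.

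- **Group 2 rule.** "Subjects should receive a total number of study drug tablets equivalent to a prednisolone dose of" 15 mg/m², with a 40 mg cap and rounding to 5 mg. This is nearly the group 1 sentence, where there is no background prednisolone to count.
- **Group 3 rule.** "Subjects should receive a total number of study drug tablets equivalent to the alternate daily prednisolone dose being received (maximum dose 60mg"), with the same rounding.
- **Group 2 examples.** The lead-in to Example 1 says tablets are given "so that the prednisolone dose received in the active treatment arm is" 15 mg/m². The background-day line is "Day 1 Prednisolone 10mg + 1 tablet of study drug", with three tablets on the other days, and the stated result is active-arm children "receiving prednisolone 15mg daily for 6 days". Example 2 has "Day 1 Prednisolone 10mg + 2 tablets of study drug". Example 3 has 10 mg of background prednisolone and no study tablets on background days.
- **Group 3 examples.** Example 1 has "Day 1 Prednisolone 20mg + 0 tablets of study drug" and four tablets on the other days. Example 2 has 25 mg and none, then five.
- **Synopsis, Treatment Description/Arms.** A child on 10 mg/m² on alternate days has the dose raised to 15 mg/m² daily by additional study tablets. In the 30 mg/m² illustration, the control child takes placebo tablets on only three of the six days.
- **Protocol 4.7.** Tablet numbers come from an online Dose Calculator and are entered on an Advice Letter to the family. The documents do not give the calculator's logic.

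**The concern.** In groups 2 and 3 the sentence that reads as the rule fixes the number of study tablets, not the total prednisolone. It has no step for prednisolone the child is already taking. The examples beneath it do have such a step, but it is never written as a formula. Someone working from the sentence and someone working from the examples would therefore arrive at different tablet counts for background days.

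Three things depend on that count: the steroid dose a child in the active arm receives, the dose contrast being tested in children on alternate-day prednisolone, and the number of required tablets. Required tablets are the denominator of the 80-120% adherence definition in SAP 5.4. Because this is a paediatric dosing rule, it should agree with its own illustrations.

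**Working it through.** **Inputs (Protocol 4.8).** D is the target: 15 mg/m² × BSA rounded to 5 mg in group 2, or the current alternate-day dose in group 3. B is the background dose on its alternate days. Study tablets are 5 mg. Whichever day the course starts, it has three background days and three other days.

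**Reading taken from the examples.** Study drug is (D − B)/5 tablets on background days and D/5 on other days. The dose is D every day, so the course total is 6D, using (6D − 3B)/5 tablets.

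**Literal rule sentence, background continued.** Study drug is D/5 tablets on all six days. The background-day dose is B + D, so the course total is 3(B + D) + 3D = 6D + 3B, using 6D/5 tablets.

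**Reproducing the plan's figures.** The first reading gives 15, 20 and 10 mg daily for group 2, and 20 and 25 mg daily for group 3. These are the results stated in the protocol. The literal reading gives none of them on background days.

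| Example | D (mg) | B (mg) | Tablets on a background day: example / literal | Dose on a background day (mg): example / literal | Six-day dose (mg): example / literal | Excess | Tablets per course: example / literal | Ratio |
|---|---|---|---|---|---|---|---|---|
| Group 2, Ex 1 (BSA 1.0) | 15 | 10 | 1 / 3 | 15 / 25 | 90 / 120 | 33% | 12 / 18 | 1.5 |
| Group 2, Ex 2 (BSA 1.2) | 20 | 10 | 2 / 4 | 20 / 30 | 120 / 150 | 25% | 18 / 24 | 1.33 |
| Group 2, Ex 3 (BSA 0.8) | 10 | 10 | 0 / 2 | 10 / 20 | 60 / 90 | 50% | 6 / 12 | 2.0 |
| Group 3, Ex 1 (BSA 1.0) | 20 | 20 | 0 / 4 | 20 / 40 | 120 / 180 | 50% | 12 / 24 | 2.0 |
| Group 3, Ex 2 (BSA 1.2) | 25 | 25 | 0 / 5 | 25 / 50 | 150 / 225 | 50% | 15 / 30 | 2.0 |

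The excess is 3B/6D = B/(2D); for group 2 Example 1 it is 10/30 = 33%.

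**Adherence.** Even the smallest tablet gap crosses the 80-120% band: 24/18 = 133% and 18/24 = 75%. In group 2 Example 1 the figures are 18/12 = 150% and 12/18 = 67%.

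**The continuation assumption.** The literal figures assume that background prednisolone carries on during the course. The rule sentences do not say so; the example schedules and Synopsis do. If study tablets replaced it instead, the active-arm total would be 6D, as in the examples. But the control arm would then lose its background dose, contrary to the Synopsis: "No change to therapy through the use of placebo study drug tablets for a total of six days".

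**Group headings.** Section 4.8 has less than and greater than 15 mg/m², so exactly 15 has no group; the Synopsis includes it in the lower category. Both rules give the same target there apart from rounding. The caps (40 and 60 mg) would separate them only above 40/15 = 2.67 m².

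**The case against.** The strongest answer is that nobody should read the sentence alone. The example lead-ins describe the dose received, every example lists tablets day by day for both start-day cases and ends with the resulting daily dose, and the Synopsis agrees. The literal figures also borrow the continuation of background prednisolone from those same examples while setting aside their tablet counts. All of this stands. It shows that the target is described as a total everywhere except in the two rule sentences, and that the conflict is one of wording. It does not make the sentences agree with the examples.

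A reader might go further and infer that children at different sites received different doses, or that a safety problem has been shown. The documents do not support that. Families receive numbers from the Dose Calculator through a filed Advice Letter. Since the calculator's logic is not given, variation between sites is conjecture.

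A reader might also infer that every child is affected after a relapse. That is too broad: children on daily prednisolone get no study drug (4.8, group 4), those off prednisolone have no background dose to count, and the protocol expects group 3 to be a minority.

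Nor does a child on a low post-relapse taper clearly fall into group 1. Relapse treatment does stop long-term maintenance (4.9), which makes the group 2 heading loose. But the group 1 text has the child taking no prednisolone after the course, and 4.8 elsewhere treats a planned reducing regimen as a change in maintenance dose.

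The analysis consequences are limited. Cumulative dose normally uses the actual tablet count and is estimated only where the count is missing (SAP 9.4). Adherence is descriptive (SAP 7.2), and the per-protocol analysis has been removed.

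**Conclusion.** The inconsistency is real and confined to wording. The rule sentences for groups 2 and 3 of Protocol 4.8, applied literally, contradict all five of their own examples and the Synopsis. Assuming background prednisolone continues, the literal reading puts the six-day active-arm dose 25% to 50% above the examples, up to a factor of two on a background day, with 1.33 to 2.0 times the required tablets. These are the sizes of a possible misreading; the documents do not show that it has occurred. The gap at exactly 15 mg/m² has essentially no dose effect, and the taper case is a matter of clearer headings. Sample size, alpha and power are unaffected. The wording should be corrected because it is a dosing rule for children and the correction is cheap.

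**What to change.** The sponsor should reconcile the rule sentences of groups 2 and 3 with their worked examples and the Synopsis, and state one formula giving study tablets on background days and on other days. The formula should say whether rounding to 5 mg applies to the total or to the study tablets: every example uses a background dose in whole 5 mg steps, so the examples do not settle this. The sponsor should then confirm that the Dose Calculator and Advice Letter follow the formula, and that required tablets in SAP 5.4 are counted the same way.

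As a minor tidy-up, align the 4.8 group headings with the Synopsis at exactly 15 mg/m², and make clear which group covers a child on a post-relapse alternate-day taper. Which dose is right is for the sponsor to decide.

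The cost is protocol wording, a calculator check and a note to sites. No new procedure and no extra patients are needed.
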